**Figure 2 f2:**
[figure not shown]
Schematic diagram of sham acupuncture.

### Observational indicators and follow-up

Baseline demographic data (age, gender, body mass index, smoking history, alcohol consumption history, place of residence, years of education, whether the only child, parents’ marital status, family’s area of residence, etc.) and disease information (age of onset, duration of disease, family history of psychiatric disorders, medication, etc.) will be collected from the participants. Participants will be followed up at 4 weeks after they have finished treatment (i.e., Week 12), either face-to-face or by telephone, to record changes in their medical condition and follow-up information. As well, they will be evaluated by CDRS-R, HAMD-17, HAMA-14, PSQI, and C-SSRS (see *Appendix1.* for details) at weeks 0, 2, 4, 6, 8 of treatment and week 12 of the follow-up period.

### Primary outcome

Difference in CDRS-R scores at weeks 0 and 8 of treatment.

### Secondary outcomes

①HAMD-17 clinical score reduction rate: Pre-treatment HAMD-17 score-HAMD-17 score after 8 weeks of treatment/Pre-treatment HAMD-17 scores.

②HAMD-17clinical remission rate: proportion of HAMD-17 scores <7 after 8 weeks of treatment.

③Difference in CDRS-R scores at weeks 0, 2, 4, 6, 8, 12.

④Difference in HAMD-17, HAMD-14, PSQI, and C-SSRS scores at weeks 0, 2, 4, 6, 8, 12.

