## Study design and methods

### Study design

This is a single-center randomized controlled trial, and participants will be assigned to receive acupuncture or sham acupuncture in a 1:1 ratio. Each participant will sign an informed consent form prior to enrollment. The protocol followed SPIRIT for TCM statement (22).

The total observation period will be 12 weeks, including an 8-week intervention period (weeks 0-8), and a 4-week follow-up period (weeks 8-12). Assessments will be conducted at baseline, week 2, week 4, week 6, week 8 and week 12. The study process is illustrated in **Figure 1**, while the schedule of enrolment, treatments, and assessments can be seen in **Table 1**.

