### Inclusion criteria

Participants who meet the following inclusion criteria will be included: (1) 12 years ≤ age <18 years; (2) Meet DSM-5 diagnostic criteria for “depressive disorders”; (3) Meet mild to moderate ADD (8≤HAMD-17 score < 20); (4) No suicide risk, “No” to all items on the C-SSRS, and a score <3 on item 3 (suicide) of the HAMD-17; (5) No medication (escitalopram, mirtazapine, etc.) or physiotherapy (transcranial magnetic stimulation, transcranial electrical stimulation, acupuncture, electroconvulsive therapy, etc.) received within the past 1 month; (6) Refuse to take the medication; (7) Good reading and writing ability, and able to communicate normally; (8) Volunteer to participate in this study and sign an informed consent form.

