### Randomization and blinding

In this study, participants will be divided into an intervention group and a control group using a block randomization method. The randomization sequence will be generated by a randomizer not involved in trial implementation and statistics with the aid of Stata software, setting a block length of 4, with the 60 participants divided into a total of 10 blocks.

The random assignment sequence and grouping results of the Stata software output will be recorded by the randomizer on paper and sealed in an opaque envelope with a number representing the order in which the participants are grouped. Envelopes will be kept by randomizer.

After the participants meet the enrollment criteria, sign the informed consent and complete the baseline data collection, the researchers will ask for a random number according to the enrollment order of the participants from randomizer, and then conduct clinical studies according to the predetermined treatment plan of each group.

Participating researchers include randomizers, therapists, assessors and statistical analysts. The study will be blinded to patients, assessors and statistical analysts. If a participant experiences a serious adverse reaction during the trial, unblinding will take place immediately. The procedure for unblinding will be the intervener explains to the trial leader the occurrence of a serious adverse reaction in the participant and requests unblinding. Data from this study will be reviewed and evaluated by the data monitoring committee (DMC), which consisted of 5–6 clinicians and statisticians independent of the sponsor and competing interests. And every three months there will be a trial monitoring by an independent clinical trial monitor.

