### Statistical considerations

#### Sample size

This trial is a pilot trial aim to preliminarily explore the possibility of acupuncture in the treatment of ADD, and to evaluate the feasibility of conducting further large-scale clinical trials to verify the efficacy of acupuncture. Moreover, the results of this trial will facilitate the calculation of an appropriate sample size for further randomized clinical trials. The minimum sample size for exploratory trials is 20 to 30 per group according to Provisions for Drug Registration in China. It is generally accepted that at least 30 participants are required for a pilot study (24). According to an estimate of the number of patients expected to participate in the trial and the minimum number of patients required to assess the practical purpose of the trial., we choose the maximum of 30 participants, and the sample size of 60 participants is determined.

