### Statistical analysis

The primary and secondary outcomes of this study will be analyzed using the modified intention to score principle. The other statistical analyses including feasibility outcomes and security outcomes. And the safety analysis will include all patients who have received at least one time of intervention.

Analyses of the primary outcomes will be conducted using linear mixed-effects models (MMRM) and generalized linear mixed models (GLMM) in repeated-measures design, which incorporate the clinical effect rates at weeks 0, 2, 4, 6, 8, and the follow-up period as response variables, as well as baseline values, time with treatment factors, time, and treatment factors as fixed-effects variables for the analyses. This study will assume that missing indicators are randomized, and due to the ability of the MMRM to cope with randomly missing data, this study will not conduct data filling for the primary outcome.

Reliability of our data will be analyzed using Cronbach’s Alpha, which is a commonly used indicator for assessing the internal consistency of a scale (25), and data assessed through the scale are considered reliable only when it is >0.7.

Three sensitivity analyses will be conducted in this study for the primary outcomes. First, the study will exclude missing data and analyzes the complete case dataset. Second, a multiple filling method will be used to fill in the outcomes before conducting the evaluation. Third, the primary outcome will be analyzed based on the set of compliant scenarios. In addition, the study will also conduct subgroup analyses of the primary outcome, which will include gender, age, hospital district, BMI, duration of disease, comorbidities, and medication use. For the analysis of secondary outcome, repeated measures information will also be based on the MMRM method; for other quantitative data outcomes, this study will use the Mann-Whitney U test or t-test, depending on whether the data are normally distributed or not.

Statistical descriptions will be carried out for the adverse reaction indicators, and the method of chi-square test or Fisher’s exact probability will be used to compare the differences between groups.

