The study will use the R programming language to carry out the statistical analysis. The test level α is 0.05, and all secondary outcome analyses as well as subgroup analyses will not be adjusted for multiple comparisons α, so the results of the evaluation of secondary outcomes and subgroup analyses will be considered exploratory.

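### The two week-8 HAMD-17 rates are not clearly given a baseline-adjusted analysis, which costs some avoidable precision at 30 per arm (minor; the crude comparisons stay valid)

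*Protocol article*

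**What the plan says.** All references are to the protocol article.

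- *Inclusion criteria*: "Meet mild to moderate ADD (8≤HAMD-17 score < 20", so entry scores run from 8 to 19.
- *Secondary outcomes*, item 1, the reduction rate: "Pre-treatment HAMD-17 score-HAMD-17 score after 8 weeks of treatment/Pre-treatment HAMD-17 scores".
- *Secondary outcomes*, item 2, remission: "proportion of HAMD-17 scores <7 after 8 weeks of treatment", so a score of 6 or less.
- *Secondary outcomes*, item 4, also lists HAMD-17 scores over weeks 0 to 12.
- *Study design*: "participants will be assigned to receive acupuncture or sham acupuncture in a 1:1 ratio". *Randomization and blinding* describes blocks of 4 and mentions no severity stratum. *Sample size*: "we choose the maximum of 30 participants, and the sample size of 60 participants is determined".
- *Statistical analysis*, primary outcome: MMRM and GLMM with clinical effect rates at each visit as the response, and baseline values among the fixed effects.
- *Statistical analysis*, secondary outcomes: MMRM for repeated measures, and "for other quantitative data outcomes, this study will use the Mann-Whitney U test or t-test". Chi-square or Fisher tests are named for adverse reactions only. Secondary results are declared exploratory.

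**The concern.** A participant's chance of ending at 6 or below depends strongly on the entry score, and the entry range is wide compared with its distance from the cut-off. Baseline HAMD-17 is therefore prognostic for remission. If it is left out of the analysis, a chance difference in entry severity between two arms of 30 goes straight into the remission difference.

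The section does not leave the matter wholly open. For the reduction rate it states a test, and that test has no baseline term. For remission it is unclear. The sentence carrying the baseline term is about the primary outcome, a CDRS-R score difference, yet its response is called a rate. The only efficacy outcomes the article calls rates are the two HAMD-17 ones. These are defined at week 8 only and cannot serve as responses at week 0: the reduction rate is zero there by construction, and nobody can be in remission at entry with a floor of 8. A reader cannot tell which outcomes receive the adjustment. At stake is precision in exploratory comparisons.

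**Working it through.** **Plan's own figure.** 2 × 30 = 60, as stated. There is no power calculation, HAMD-17 SD, slope or remission rate to reproduce, so everything below that needs one rests on an assumption.

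**From the documents alone.**
- Fall needed to remit from entry 8: 8 − 6 = 2 points, 2/8 = 25%.
- Fall needed from entry 19: 19 − 6 = 13 points, 13/19 = 68%.
- One point on the reduction rate: 1/8 = 12.5% at entry 8, 1/19 = 5.3% at entry 19.

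**How prognostic baseline could be.** Assume entry uniform on 8 to 19 (mean 13.5), week-8 mean 9, slope b, residual SD s. Then P(remission) ≈ Φ((6.5 − [9 + b(entry − 13.5)])/s).
- b = 0.5, s = 4: entry 8 gives Φ(0.25/4) = 52%; entry 19 gives Φ(−5.25/4) = 9%.
- b = 0.7, s = 3.5: entry 8 gives Φ(1.35/3.5) = 65%; entry 19 gives Φ(−6.35/3.5) = 3%.

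**Size of chance imbalance.** The variance of a uniform integer on 8 to 19 is (12² − 1)/12 = 11.92, so SD 3.45. The SE of the difference in baseline means is 3.45 × √(2/30) = 0.89 points. With a clipped normal (mean 14, SD 3), simulation gives about 0.7.

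**Simulation of remission.** 30 per arm, 3,000 trials per scenario, no dropout. The stated level is "The test level α is 0.05"; two-sided is assumed. The mean fall is 30% or 40% of baseline and the residual SD is 3 or 4. The crude test is a two-proportion z-test and the adjusted test is a logistic likelihood-ratio test with baseline HAMD-17. The adjusted SD comes from a linear regression of remission on treatment and baseline. Variance cut = 1 − (adjusted SD/crude SD)².

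With a 3-point treatment effect:

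| Baseline | Fall | Residual SD | Crude SD | Adjusted SD | Variance cut | Crude power | Adjusted power | Gain (points) |
|---|---|---|---|---|---|---|---|---|
| uniform | 30% | 4 | 0.121 | 0.111 | 16% | 46.2% | 54.3% | 8.1 |
| uniform | 40% | 4 | 0.124 | 0.117 | 11% | 53.0% | 60.8% | 7.8 |
| uniform | 40% | 3 | 0.122 | 0.108 | 22% | 70.9% | 81.0% | 10.1 |
| normal | 30% | 4 | 0.122 | 0.115 | 11% | 51.6% | 58.0% | 6.4 |
| normal | 40% | 4 | 0.125 | 0.120 | 8% | 54.5% | 59.9% | 5.4 |
| normal | 40% | 3 | 0.123 | 0.115 | 13% | 75.7% | 83.1% | 7.4 |

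The mean risk difference hardly moves with adjustment (first row: 0.235 crude, 0.234 adjusted). Across all scenarios, each 1-point imbalance shifts the crude difference by 4.5 to 6.6 percentage points.

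With no treatment effect, the mean crude difference lies between −0.005 and +0.004. Type I error is 4.6 to 5.3% crude and 5.2 to 6.0% adjusted. The Monte Carlo SE is √(0.05 × 0.95/3000) = 0.4 points, so the adjusted test may run slightly above nominal and a little of its power gain may come from that. The variance cut is the cleaner measure.

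With a 2-point effect and the slope model above, power moves from 21–26% to 26–31%. A separate simulation under assumed SDs and slopes put the gain for remission at about 2 to 13 points.

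**Reduction rate.** Baseline-adjusted analysis of the score against a t-test on percentage change, with a 2- or 3-point effect, gains about 1 to 3 points of power.

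**The case against.** The case for leaving the plan alone is substantial, and most of it stands.

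- A reader might infer from the 25% versus 68% contrast that the remission comparison partly measures entry severity instead of treatment. It does not. Allocation is randomised 1:1, entry severity is balanced in expectation, and the simulated crude comparison is unbiased with close to its nominal error rate. The shift per point of imbalance is conditional on an imbalance; it is not bias.
- A reader might infer that the cut-off is badly placed. Any fixed remission threshold asks for a larger fall from a higher entry score; that is what a state-based endpoint does.
- A reader might infer that remission is to be tested by t-test or Mann-Whitney. The sentence is limited to quantitative outcomes, and remission is binary. Naming no test for a binary exploratory outcome is something an article may leave to the analysis plan, and is not counted here.
- The generalised mixed model with baseline values may already be intended for remission. That possibility cannot be excluded, but the wording does not establish it.
- The reduction rate is already divided by each participant's own baseline, and an adjusted HAMD-17 contrast appears to be available from the MMRM for item 4. This is why the gain for that outcome is so small.

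What survives is narrow: a stated unadjusted test for the reduction rate, and a modelling sentence whose response does not match its outcome.

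**Conclusion.** The point holds as a minor, free improvement. The crude comparisons are valid. Leaving out baseline HAMD-17 forgoes roughly 6 to 22% of the variance of the remission difference across the scenarios simulated (lowest 1 − (0.118/0.122)² = 6%, under no effect; highest 22%, in the table). In power this is about 2 to 13 points for remission and 1 to 3 for the reduction rate. These figures depend on assumed baseline distributions, slopes, residual SDs and effects, and on complete follow-up; none of the values comes from the article.

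The outcomes are exploratory in a pilot with no power calculation, which limits the importance further. It is tempting to add that noisy remission rates would mislead the sizing of the later trial. The *Sample size* section says only that the results will help with that calculation. It does not say that remission rates will be used, and the primary outcome is CDRS-R.

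**What to change.** In *Statistical analysis*:

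1. State that week-8 remission is analysed by a logistic model with treatment and baseline HAMD-17, reported as a standardised risk difference with 95% CI beside the crude proportions.
2. Base inference on HAMD-17 reduction on the week-8 contrast of the HAMD-17 MMRM planned for secondary outcome 4, stating that baseline HAMD-17 is a covariate. Keep the percentage reduction as description.
3. Define the clinical effect rates, and say which outcome they and the generalised mixed model refer to.

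The remission cut-off needs no change. The cost is a few sentences; baseline HAMD-17 is already scheduled for every participant, so there is no extra data collection.

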### Feasibility outcomes

①Proportion of participants who completed the required 8-week acupuncture treatment. If≥80% participants completed, proceed; if 50%-80% participants completed, modify protocol; if <50% participants completed, do not proceed.

②Rate of drop-out during treatment. If rate of drop-out ≤ 20%, proceed; if rate of drop-out is 20%-50%, modify protocol; if rate of drop-out>50%, do not proceed.

③Response rate. Response rate of participants to the collected indicators will be evaluated at pre-therapy, post-therapy, and 4 weeks after treatment.

④Blinding test. All the participants will be tested for the success of blinding after the final treatment session. They will be asked to judge whether they have received real acupuncture or sham acupuncture, and we will use the Bang’s blinding indices to assess the adequacy of blinding (23).

⑤Satisfaction. Participants’ satisfaction with the intervention will be ranked on a 5-point scale, each point is very satisfied, satisfied, neutral, dissatisfied, and very dissatisfied.

### Security outcomes

The outcomes of safety evaluation will be recorded, including basic vital signs (blood pressure, respiration, pulse, etc.) before and after treatment, and records of adverse events (AEs) during treatment and follow-up.

Classification of AEs: Serious Adverse Events (SAEs) are adverse medical events such as death, life-threatening, permanent or severe disability or loss of function, subjects requiring hospitalization or prolonged hospitalization, and congenital anomalies or birth defects that occur in the course of a clinical trial. Significant adverse events are defined as any occurrence of AEs other than SAEs that result in the use of targeted medical measures (e.g., cessation of needling, symptomatic treatment) and significant abnormalities in hematology or other laboratory tests. An unintended adverse event (UAE) is an AE that is of a different nature, severity, or frequency than the expected risk described in a previous protocol or other relevant information (e.g., investigator’s brochure, drug insert).

Handling of AEs: When a participant has trial-related AEs, including clinically significant abnormalities in laboratory tests, the participant should be assured of appropriate medical treatment, such as stopping the needling, decreasing the frequency, or symptomatic treatment. At the same time, to avoid more serious consequences of the clinical trial, the researcher should decide whether to terminate or suspend the clinical trial in order to protect the rights and safety of the participants.

Recording of AEs: Medical documents related to AE, including request forms for laboratory tests and report forms for test results, should be kept in the original files, and the original records should be kept true, accurate, and complete. All records should be signed and dated by the researcher. The content of AE record includes the name of the AE described in medical terminology, clinical signs/symptoms, start and end time of occurrence, severity, measures taken, and the outcome, etc., and the relevance to the trial protocol should be judged. Measures taken mainly include: no measures taken, adjustment of trial parameters, cessation of needling, combination of medications, hospitalization, or prolongation of hospitalization, etc. AE outcomes are mainly cured, improved, not cured, worsened, died, lost to visit, or unknown.

### Statistical considerations

#### Sample size

This trial is a pilot trial aim to preliminarily explore the possibility of acupuncture in the treatment of ADD, and to evaluate the feasibility of conducting further large-scale clinical trials to verify the efficacy of acupuncture. Moreover, the results of this trial will facilitate the calculation of an appropriate sample size for further randomized clinical trials. The minimum sample size for exploratory trials is 20 to 30 per group according to Provisions for Drug Registration in China. It is generally accepted that at least 30 participants are required for a pilot study (24). According to an estimate of the number of patients expected to participate in the trial and the minimum number of patients required to assess the practical purpose of the trial., we choose the maximum of 30 participants, and the sample size of 60 participants is determined.

### Statistical analysis

The primary and secondary outcomes of this study will be analyzed using the modified intention to score principle. The other statistical analyses including feasibility outcomes and security outcomes. And the safety analysis will include all patients who have received at least one time of intervention.

Analyses of the primary outcomes will be conducted using linear mixed-effects models (MMRM) and generalized linear mixed models (GLMM) in repeated-measures design, which incorporate the clinical effect rates at weeks 0, 2, 4, 6, 8, and the follow-up period as response variables, as well as baseline values, time with treatment factors, time, and treatment factors as fixed-effects variables for the analyses. This study will assume that missing indicators are randomized, and due to the ability of the MMRM to cope with randomly missing data, this study will not conduct data filling for the primary outcome.

Reliability of our data will be analyzed using Cronbach’s Alpha, which is a commonly used indicator for assessing the internal consistency of a scale (25), and data assessed through the scale are considered reliable only when it is >0.7.

Three sensitivity analyses will be conducted in this study for the primary outcomes. First, the study will exclude missing data and analyzes the complete case dataset. Second, a multiple filling method will be used to fill in the outcomes before conducting the evaluation. Third, the primary outcome will be analyzed based on the set of compliant scenarios. In addition, the study will also conduct subgroup analyses of the primary outcome, which will include gender, age, hospital district, BMI, duration of disease, comorbidities, and medication use. For the analysis of secondary outcome, repeated measures information will also be based on the MMRM method; for other quantitative data outcomes, this study will use the Mann-Whitney U test or t-test, depending on whether the data are normally distributed or not.

Statistical descriptions will be carried out for the adverse reaction indicators, and the method of chi-square test or Fisher’s exact probability will be used to compare the differences between groups.

The study will use the R programming language to carry out the statistical analysis. The test level α is 0.05, and all secondary outcome analyses as well as subgroup analyses will not be adjusted for multiple comparisons α, so the results of the evaluation of secondary outcomes and subgroup analyses will be considered exploratory.

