**Methods:**

In this pilot randomized controlled trial, 60 participants will be randomly assigned to receive acupuncture or sham acupuncture for 8 weeks of treatment and 4 weeks of follow-up. The primary outcome will be the difference in Children’s Depression Rating Scale-revised (CDRS-R) scores at weeks 0 and 8 of treatment. Secondary outcomes will include 17-item Hamilton Depression Scale (HAMD-17) clinical score reduction rate and clinical remission rate, difference in CDRS-R scores, HAMD-17 scores, 14-item Hamilton Depression Scale (HAMD-14) scores, Pittsburgh Sleep Quality Index scale (PSQI) scores, and Columbia-Suicide Severity Rating Scale (C-SSRS) scores. All outcomes will be assessed at weeks 0, 2, 4, 6, 8 of treatment and week 12 of the follow-up period. In addition, we will assess the safety outcomes from baseline to the end of this trial and feasibility outcome after treatment.

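### The stated response of the primary analysis, an undefined rate modelled from week 0, does not match the declared CDRS-R outcome, and two models are named for it without saying which decides

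*Protocol article*

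**What the plan says.** **Outcome.** The Primary outcome section of the protocol article reads "Difference in CDRS-R scores at weeks 0 and 8 of treatment". The abstract agrees: "The primary outcome will be the difference in Children’s Depression Rating Scale-revised (CDRS-R) scores at weeks 0 and 8 of treatment". This is a continuous score with a single endpoint visit.

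**Analysis.** The Statistical analysis section opens with "Analyses of the primary outcomes will be conducted using linear mixed-effects models (MMRM) and generalized linear mixed models (GLMM) in repeated-measures design". It then gives the response, "which incorporate the clinical effect rates at weeks 0, 2, 4, 6, 8, and the follow-up period as response variables", and the model terms, "as well as baseline values, time with treatment factors, time, and treatment factors as fixed-effects variables for the analyses". The same section relies on the MMRM to handle missing primary-outcome data and says that repeated secondary measures also go to an MMRM.

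**Rates that are defined.** Under Secondary outcomes there are two efficacy rates, both on HAMD-17 and both at week 8. One is the proportional score reduction. The other is remission, "proportion of HAMD-17 scores <7 after 8 weeks of treatment". CDRS-R at all six time points is listed there too, as a separate secondary outcome.

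**Entry range.** The third inclusion criterion is "Meet mild to moderate ADD (8≤HAMD-17 score < 20".

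**Error level.** The test level is 0.05, and only secondary and subgroup results are labelled exploratory.

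**The concern.** The sentence that fixes the primary analysis names a response variable, and it is not the declared primary outcome. A rate is not a score difference. No CDRS-R rate exists in the article, and the rates that do exist belong to another scale and to the secondary outcomes. An analyst following the text must guess what to put on the left-hand side of the model.

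Two further features of the sentence add to this. An MMRM and a GLMM are both named for what is one continuous outcome, without saying which gives the primary result. Week 0 is listed among the responses although baseline values are already a covariate.

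At stake is the identity of the primary estimate. The Sample size section says the results will help to calculate the sample size of later randomised trials. For that, the estimate has to be a CDRS-R difference at week 8 from one model settled in advance.

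**Working it through.** The article gives no figure on this point to reproduce. The total of 60 is 2 × 30 by pilot convention, with no effect size, standard deviation or power. The check is therefore one of consistency, taking each plausible meaning of the response in turn.

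**1. The response is a HAMD-17 rate.**
- Inputs: HAMD-17 at entry is at least 8 and below 20 (Inclusion criteria); remission is a score below 7 (Secondary outcomes).
- Remission at week 0: no score from 8 to 19 is below 7, so the rate is 0% in both groups.
- Reduction at week 0, reading the formula as (pre − post) / pre: (pre − pre) / pre = 0 for every participant.
- Result: both rates are constants at week 0. A logistic GLMM for remission with a week-0 level has no finite estimate for that level. Both rates are also secondary and defined at week 8 only, so this reading replaces the primary outcome with another variable.

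**2. The response is the CDRS-R score.** Write Y(i,t) for participant i at visit t, T(i) for treatment, and the stated terms as

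Y(i,t) = μ(t) + τ(t)·T(i) + β·Y(i,0) + e(i,t).

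- At t = 0 the left-hand side is Y(i,0), which is also the covariate. Setting β = 1, μ(0) = 0 and τ(0) = 0 makes e(i,0) = 0 for everyone.
- With an unstructured covariance (an assumption; the article names none), the week-0 residual variance can shrink to zero and the likelihood has no maximum.
- With complete data and compound symmetry (also assumed), the model can be fitted. The common slope is then the mean of the visit-specific slopes. Week 0 contributes exactly 1, so β = (1 + 5b) / 6, where b is the mean slope over the five post-baseline visits. Unless b is already 1, week 0 pulls the baseline adjustment towards 1. Randomisation still protects the group contrast from bias, but the adjustment is not the intended one.

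**3. The response is the change in CDRS-R.** At week 0 it is Y(i,0) − Y(i,0) = 0 for everyone, again a constant.

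Under all three readings week 0 cannot usefully be a response while baseline is a covariate.

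**4. Two model families.** If each model were tested at 0.05 and either result could be claimed, the chance of at least one false positive would be 1 − 0.95² = 0.0975 under independence, and less with positive correlation, which is expected because both use the same data. The article does not say that either may be claimed. This is a ceiling on what the ambiguity could cost, not the plan's error rate.

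**5. Does the repair keep the declared outcome?** Drop week 0 from the response and subtract Y(i,0) from both sides:

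Y(i,t) − Y(i,0) = μ(t) + τ(t)·T(i) + (β − 1)·Y(i,0) + e(i,t).

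The treatment effect τ(8) is unchanged. An MMRM of post-baseline scores adjusted for baseline therefore estimates the between-group difference in change from week 0 to week 8.

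**The case against.** The strongest reply is that this is loose wording. The sentence is introduced as the analysis of the primary outcomes, includes week 8, names a linear mixed model, and is followed by a missing-data statement that makes sense for a continuous score under MMRM. Other phrases in the section are equally loose. A statistical analysis plan, not shown here, may settle the matter.

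Much of this stands, and several stronger inferences should be resisted:
- A reader might infer that the declared outcome will not be analysed at all. The article does not establish that; it shows an undefined response that conflicts with the declared outcome.
- A reader might object to modelling all visits, or infer that the effect is averaged over them and so diluted. The article never says effects are averaged, and it lists a treatment-by-time term from which a week-8 difference can be taken.
- A reader might infer that the score is dichotomised, with a loss of information or power. No passage dichotomises CDRS-R, and the HAMD-17 reduction rate is itself continuous.
- A reader might call the primary model degenerate outright because week-0 rates are constant. That holds only if the response is a HAMD-17 rate, and the sentence does not mention HAMD-17.
- The absence of a named week-8 contrast would, on its own, be detail for the analysis plan.

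What the reply does not remove is the stated text. Reading rates as scores still leaves week 0 as both response and covariate, and still leaves two model families for one continuous outcome. These are things the article says, not things it leaves out.

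**Conclusion.** The point holds as an inconsistency in the current text. The response stated for the primary analysis is undefined and does not match the declared CDRS-R outcome, the MMRM and GLMM are named together without ranking, and week 0 is on both sides of the model. No reading examined makes the sentence workable exactly as printed.

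The size is moderate. No number in the article changes. The trial is a pilot without a power calculation, and its explicit proceed, modify or stop thresholds apply to treatment completion and drop-out, not to this test. The harm would be an unclear or wrong primary estimate carried into planning a later trial. No loss of power or dilution of effect can be quantified from the article, because it states neither averaging over visits nor dichotomising. The likelihood and slope results in the working depend on the covariance structures assumed there. The constancy of the rates and of the change score at week 0 needs no such assumption.

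**What to change.** Replace the sentence on the primary analysis with text along these lines:

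*The primary analysis is an MMRM with CDRS-R total score at weeks 2, 4, 6, 8 and 12 as the response, and treatment, visit, treatment-by-visit and baseline CDRS-R as fixed effects. The primary estimate is the between-group difference at week 8, with its 95% confidence interval.*

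Keep baseline as a covariate only, and delete the reference to effect rates. Reserve the GLMM, with a logit link, for binary HAMD-17 remission at post-baseline visits. If only week 8 is analysed there is one observation per participant, and ordinary logistic regression is enough.

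The cost is a change of wording. Visits, measurements and sample size stay as they are. It should be made before any unblinded data are seen, and any separate analysis plan should carry the same text.
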